### Sample Size

The sample size was calculated using a G*power of 3.1.4. The effect size was calculated as 0.28 based on the BBS from a study reported by Koch et al. (2018). To achieve 95% power with an alpha error of 5%, a sample size of 30 patients will be required. Allowing for a dropout rate of 20%, at least 38 patients are necessary. To ensure enough power to detect this typical difference, we will aim to recruit 40 patients (20 patients per group).

### Randomization

All participants will be prestratified into two subgroups (i.e., poor balance on 0–20 scores vs. acceptable balance on 21–40 scores) on the basis of their balance function to ensure a relatively even distribution between groups (Lisa and Nicol, 2008) (Figure 2). After obtaining informed consent, a random sequence will be generated using the computer, 40 participants will be randomly allocated in a 1:1 ratio to each group and will receive either real or sham iTBS. The advantage of this type of assignment process, which is designed in our study, is that detect effects can be improved especially for studies involving small samples.

**FIGURE 2 F2:**
[figure not shown]
Flow chart of random grouping procedure.

### Blind

This study is a participants and assessors-blinded study. Given the nature of the iTBS intervention, blinding the physicians performing the intervention is impossible. The intervention team needs to be separated into blinded physicians performing routine rehabilitation treatment, and unblinded physicians exclusively applying iTBS. However, patients, outcome assessors, research assistants, and statisticians will be blinded. For urgent unblinding, researchers can use sealed envelopes labeled with the patients’ randomization numbers. To maintain the quality of the trial, a patient’s allocation must be unblinded only in exceptional circumstances when knowledge of the actual treatment is essential for the management of the patient.

### Intervention

Patients recruited in this study will receive a 60 min routine rehabilitation treatment immediately after completing real or sham iTBS therapy. The rehabilitation program focuses on the exercise designed to promote recovery of balance function, including trunk control, weight bearing, task oriented intervention, and balance training, which will be designed by physicians according to the patient’s balance function. Patients in both groups will be required to attend 15 sessions [one session per day, five times per week (Monday to Friday) for three consecutive weeks]. Enrollment, intervention, and assessment procedures are shown in Figure 3.

**FIGURE 3 F3:**
[figure not shown]
Schedule of participant enrollment, interventions, and assessments. BBS, Berg Balance Scale; FMA-LE, lower extremity of the Fugl–Meyer assessment; MBI, modified Barthel index; fMRI, functional magnetic resonance imaging.

Cerebellar iTBS: We use the Magneuro 100 (Vishee Medical Technology Co., Ltd., Nanjing, China) equipped with a double-cone coil (each coil is 70 mm in diameter) to stimulate the cerebellum vermis. iTBS is performed by the physician in accordance with the TMS guidelines (Groppa et al., 2012; Klooster et al., 2016). Before intervention, active motor threshold (AMT) for the tibialis anterior muscle in the unaffected side will be measured. The AMT is defined as the minimum output of stimulation that produced a motor evoked potential (MEP) of >200 μV in at least 5 out of 10 trials with 10% maximal voluntary contraction (Liao et al., 2020). Stimulation will be administered at 80% of AMT. The iTBS paradigm consisting of three pulses at 50 Hz repeated at 5 Hz frequency will be used, with 8-s rest after each 2-s stimulus, generating a total of 600 pulses in 200 s. The coil will be positioned tangentially to the scalp over the cerebellum vermis (at 1 cm below the highest point of the occipital protuberance) (Cattaneo et al., 2014; Tan et al., 2021). Sham iTBS will be performed with a customized sham coil and at the same location, frequency and intensity so that all participants are exposed to a similar clicking noise.

### Outcome Assessment

#### Primary Outcome

The BBS is a clinical test commonly used to assess the patients’ static and dynamic balance performance and can determine whether a patient is at risk of falls with an inter-rater reliability of 0.98 (Maeda et al., 2015; Meseguer-Henarejos et al., 2019). The BBS consists of 14 items, and the score for each item is 0–4 points with an overall score of 0–56 points. Good completion results in high score.

#### Secondary Outcomes

In addition to the BBS scores, FMA-LE, MBI, and rs-fMRI will be measured with the following tests.

Fugl–Meyer assessment of the lower extremity has been widely used in the assessment of the motor function of patients with stroke and has good prediction, reliability, and sensitivity to interventions (Balasubramanian et al., 2016). In addition, the reliability of the FMA scale is >75% between different raters and >88% within the same rater (Hernández et al., 2021). The FMA-LE consists of 17 items, with each item scoring a minimum of 0 and a maximum of 2 points, resulting in a maximum total score of 34 points. A high score results in good motor function of the lower extremity.

The MBI, one of the main scales used to measure the patients’ abilities to perform activities of daily living, has a reliability of 88% in patients with ischemic stroke (Yang et al., 2021). The MBI consists of 10 items, with a full score of 100 points. A high score results in good independence of the patient’s life.

All subjects will undergo rs-fMRI scans. Regional homogeneity (ReHo), fractional amplitude of low-frequency fluctuation (fALFF), and functional connectivity (FC) will be calculated to measure the local and global FC networks related to motion function. All images will be acquired by professional personnel in a 3.0T, 8-channel MRI scanner (Siemens Skyra, Germany). During scanning, subjects will be required to keep awake, breathe quietly, lie flat on the bed, fix their heads to minimize the movement of their heads and other parts, and try not to do any active thinking activity. It will take approximately 40 min to complete the test. Conventional T1 structural image parameters are as follows: repetition time (TR) = 2,000 ms, echo time (TE) = 20 ms, field of view (FOV) = 240 mm × 240 mm, slice thickness = 4 mm, slice spacing = 4 mm, flip angle (FA) = 90°, and 36 slices. Functional images will be acquired using T1-weighted gradient echo planar imaging (EPI) sequence in the axial plane with the following parameters: TR = 2,000 ms, TE = 30 ms, FOV = 240 mm × 240 mm, slice thickness = 4 mm, FA = 90°, and 35 slices.

### Statistical Analysis

#### Clinical Data Analysis

The SPSS (version 22.0, Chicago, IL, United States) statistical software will be used for data analysis. The difference will be considered statistically significant when the *P*-value ≤ 0.05 in two-tailed test. The assumption of normality will be verified by normal probability plots and the Shapiro–Wilk test. Continuous variables with normal distribution will be described as the mean (standard deviation) and analyzed by an independent-samples *t*-test. For abnormally distributed variables, the data will be described as medians with ranges and compared by Mann–Whitney U test (non-parametric tests). Categorical variables will be expressed as frequency (percentage) and Chi-square test or Fisher’s exact test will be used. Repeated measures analysis of variance (ANOVA) will be used to analyze value changes of BBS, FMA-LE, and MBI across four testing time points (weeks 0, 1, 2, and 3). When the interaction is significant, *post hoc* analysis will be conducted, and the Bonferroni adjustment will be used for paired comparisons. Data on clinical scales will be based on per-protocol (PP) and intention-to-treat (ITT) analyses (Sanchez and Xun, 2010). The PP is usually defined as subjects who complete at least 80% of the treatment protocol (Zhao et al., 2021). An ITT analysis include all the patients recruited in the study, irrespective of whether they completed the study period or not. The missing values will be imputed using a multiple imputation method.

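### Randomisation is stratified on baseline BBS, but the primary analysis treats baseline as a fourth outcome level instead of conditioning on it: a valid test, at some avoidable cost in efficiency

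*Protocol article*

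**What the plan says.** In the protocol article, the Randomization section reads: "All participants will be prestratified into two subgroups (i.e., poor balance on 0–20 scores vs. acceptable balance on 21–40 scores". It gives two purposes: an even distribution between the arms, and the advantage that "detect effects can be improved especially for studies involving small samples". The Discussion adds the motive, which is the wide spread of balance function among eligible patients (entry BBS 0 to 40).

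The Clinical Data Analysis section fixes the longitudinal analysis: "Repeated measures analysis of variance (ANOVA) will be used to analyze value changes of BBS, FMA-LE, and MBI across four testing time points", listed as weeks 0, 1, 2 and 3. Post hoc Bonferroni comparisons follow if the interaction is significant. Other continuous comparisons use an unadjusted t-test or Mann–Whitney test. No model in the article contains the stratum or a baseline covariate.

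The Sample Size section says "The effect size was calculated as 0.28 based on the BBS" and "To achieve 95% power with an alpha error of 5%, a sample size of 30 patients will be required".

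**The concern.** The model is stated, not left open, and it makes no explicit use of the factor on which randomisation is stratified. Baseline BBS is measured in everyone and is likely to be the strongest predictor of later BBS. Yet it enters only as a level of the outcome at which no treatment effect can exist. If the group-by-time test uses that information less well than a covariate would, a trial of 40 patients gives up precision that its own data could supply free of charge. At stake is the width of the interval for the BBS difference, and power if the true effect is smaller than planned.

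**Working it through.** **Inputs from the document.** Effect size 0.28; 95% power; alpha 5%, with significance set at P "≤ 0.05 in two-tailed test"; 30 evaluable patients; 40 recruited, 20 per arm; four time points including baseline.

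**Assumptions, because the document gives none.** 0.28 is Cohen's f; correlation r between visits of 0.5 to 0.9; compound symmetry; sphericity (epsilon = 1); effect profile over weeks 1 to 3 mainly linear, p = (1/3, 2/3, 1).

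**Step 1: reproduce the plan's figure.** For a group-by-time interaction with k = 2 groups and m = 4 times, λ = f²·N·m/(1−r), df1 = (k−1)(m−1) = 3 and df2 = (N−k)(m−1). With f = 0.28, r = 0.5 and N = 30, λ = 0.0784 × 30 × 4/0.5 = 18.8 and df2 = 84, so power is 95.9%. At N = 28 it is 94.4%. The stated 30 is reproduced, and 30/0.8 = 37.5 matches: "Allowing for a dropout rate of 20%, at least 38 patients are necessary". With three time points the same formula needs 36, and with two it needs 44. So under these settings the sizing also counts baseline as one of four outcome levels.

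**Step 2: the two tests on equal terms (3 df each).** Take variance 1 at each visit and an arm difference Δ at week 3.
- Planned test: it works on changes from baseline, whose covariance is (1−r)(I+J), where I is the 3×3 identity and J the matrix of ones. λ = (N/4)·Δ²·A/(1−r), with A = p′(I+J)⁻¹p = 14/9 − 4/4 = 0.556.
- Weeks 1 to 3 given baseline: the covariance is (1−r)(I+rJ). λ = (N/4)·Δ²·B/(1−r), with B = 14/9 − 4r/(1+3r).

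| r | B | information ratio B/A |
|---|---|---|
| 0.5 | 0.756 | 1.36 |
| 0.8 | 0.614 | 1.11 |
| 0.9 | 0.583 | 1.05 |

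For an effect that is complete at week 1 the ratios are 1.60, 1.18 and 1.08. For an effect at week 3 only they are 1.07, 1.02 and 1.01.

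**Step 3: power at 20 per arm, Δ = 0.56 SD, linear.**
- r = 0.5: planned λ = 10 × 0.3136 × 0.556/0.5 = 3.48, power 31%. Adjusted λ = 4.74, power 41%.
- r = 0.8: planned λ = 8.71, power 68%. Adjusted λ = 9.63, power 73%.

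**Step 4: at the plan's own effect.** The deviations of (0, 1/3, 2/3, 1) from their mean have mean square 0.139, so f = (Δ/2)·√0.139 = 0.186Δ. Thus f = 0.28 means Δ of about 1.5 SD at week 3 when r = 0.5. At N = 30, adjustment raises power from 95.9% to 99.2%, and N for 95% power falls from 30 to 22. When the effect is rescaled so that the planned test keeps its 95.9%, that N is 28 at r = 0.8 or 0.9. If the true effect is 70% of this planned size, power at N = 30 is 70.0% as planned, against 83.9% adjusted at r = 0.5, 74.8% at 0.8 and 72.3% at 0.9.

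**Step 5: separate the covariate from the contrast.** At 20 per arm, 0.56 SD, linear, r = 0.8: planned omnibus test 68%; baseline-adjusted 3-df test 73%; week-3 ANCOVA 82%; unadjusted 1-df linear trend 83%. Most of the distance from 68% to 82% comes from replacing a 3-df test with a 1-df contrast, which needs no baseline covariate.

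**The case against.** The strongest reply is that baseline is already used. A group-by-time interaction over weeks 0 to 3 compares changes, so any stable difference between patients cancels, including the stratum main effect. A reader might infer that the planned analysis ignores baseline and leaves chance imbalance uncorrected. The documents do not support that for the interaction test; it would describe only an unadjusted comparison of follow-up scores. For the same reason, the variance saving of ANCOVA over a raw follow-up t-test is the wrong measure here. Against a change score at one visit, the ANCOVA variance ratio is (1+r)/2, a saving of 25%, 10% and 5% at r = 0.5, 0.8 and 0.9.

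Three further points stand. First, the short 3-week horizon, the wide entry range and the cited inter-rater reliability of 0.98 make a high correlation at least as plausible as 0.5, and the gain is then small. Second, the even distribution between arms is delivered by the design itself without any model term, and adding the stratum only as a main effect would leave the interaction test essentially unchanged. Third, the Discussion wants to explore when the effect first appears, which a test over all visits serves.

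What remains is that a change-type comparison is less efficient than conditioning on baseline whenever r < 1, apart from about one degree of freedom, under the covariance model used here.

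**Conclusion.** The point holds as a recommendation on efficiency, not as an error. With a linear effect under compound symmetry, the gain in information is about 36%, 11% or 5% at r = 0.5, 0.8 or 0.9. It is larger for an early effect and close to nil for one that appears only at week 3.

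A reader might go on to infer that the trial is underpowered. The documents do not support this: under default settings the planned test meets its 95% target at 30 patients, and the lower powers at 0.56 SD belong to an effect well below the one used for sizing. Nor should the whole gap between the omnibus test and a week-3 ANCOVA be put down to baseline handling, as step 5 shows. Nor is there a fault in the statement "The missing values will be imputed using a multiple imputation method" beside a repeated-measures ANOVA: imputation supplies complete visits, and the pooling rule is normally a matter for the analysis plan.

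**What to change.** Analyse BBS, and likewise FMA-LE and MBI, at weeks 1, 2 and 3 with a linear mixed model. It should contain arm, week, arm by week, the continuous baseline score with baseline by week, and the BBS stratum, with an unstructured within-patient covariance. Report the baseline-adjusted arm difference at each week with its 95% CI. This still serves the aim of seeing when an effect appears.

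Whether to name week 3 as the primary contrast is a separate choice, to be made before unblinding. It gains power if the effect grows over time. It can lose to the omnibus test if the effect is complete by week 1: about 70% against 81% in simulation at 20 per arm, 0.56 SD and first-order autoregressive correlation 0.9.

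The cost is a change of wording and one or two degrees of freedom at each week. All the variables are already collected.

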#### Functional Magnetic Resonance Imaging Data Analysis

On the MATLAB R2013b (Mathworks, Natick, MA, United States) platform, the statistical parametric graph software (SPM12.0^1^) and data processing assistant for rs-fMRI software (DPARSF^2^) will be used for data processing and analysis. DPARSF is a SPM-based rs-fMRI data processing software (Yan et al., 2016). Preprocessing steps include (Lv et al., 2018; Ll et al., 2020): (a) removing the first 10–20 time points and slice timing, (b) head movement correction (head movement exceeding 2 mm in any direction or head rotation exceeding 2° will be ruled out), (c) normalization (in accordance with the Montreal Neurological Institute EPI template, each voxel is resampled to 3 mm × 3 mm × 3 mm), (d) delinear drift, (e) removal covariate (confounding effects of head movement parameters, white matter, and cerebrospinal fluid signals), (f) filter (0.01–0.1 Hz), and (g) smooth (8 mm full-width half-maximum Gaussian). Then, the ReHo, fALFF, and FC values will be calculated. The ReHo analysis is a voxel-based measurement that calculates the Kendall coefficient of concordance between a voxel and its surrounding 26 voxels, which is the ReHo value of that voxel (Zang et al., 2004). The ReHo analysis determines the synchrony of adjacent regions, and high values indicate high consistency of regional brain activity. The ALFF measurement is the root mean square of the power spectrum of the BOLD signal in the range of 0.01–0.1 Hz for each voxel. Afterward, the ALFF value of each voxel divided by the full-band ALFF sum is the fALFF value, which can reflect the strength of brain self-activity (Toole et al., 2005). FC was examined by using a seed voxel correlation approach. The cerebellar vermis will be selected as the seed region based on the stimulation target. In SPM12, after bandpass filtering and linear-trend removal, a reference time series for the seed will be extracted by averaging the fMRI time series of voxels. Then, correlations will be computed between the seed reference and the rest of the brain in a voxelwise manner. Finally, an individual relativity value (*r*-value) map will be created, and the correlation coefficients in each voxel will be transformed to *z* values by using Fisher’s *r*-to-*z* transformation to improve normality before performing random effect *t*-tests. The AlphaSim will be used for correction to obtain the adjustment statistical threshold value of *P* < 0.05. Data will be analyzed by the independent-samples (between-group comparison) or paired (within-group comparison) *t*-test.

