## Discussion

This 3-week randomized controlled clinical trial aims to study whether cerebellar vermis iTBS can improve balance function in patients with stroke. In this perspective of experiment design, our study puts forward some methodological concerns that should be discussed, including the large variation in balance function among enrolled patients. Therefore, a stratification approach will be adopted in this study to divide all participants into two subgroups in accordance with the BBS. In addition, we set a sham stimulation group to eliminate the placebo effect of iTBS intervention. After careful consideration of all factors, including the feasibility of the study and the treatment time pattern of the hospital where the experiment will be conducted, we set sessions from Monday to Friday for 3 weeks. Also, outcome will be evaluated at pre-intervention, the end of first, second, and third week of post-intervention. We want to compare the efficacy at different time points, and to explore the earliest time when the treatment can take effect. Our study will use rs-fMRI rather than task state fMRI for measuring the iTBS-induced effects, although task state fMRI can reflect the fMRI images of the brain when performing specific tasks. What we considering is that our subjects are post-stroke patients with motor dysfunction, there may be great differences in the quality of tasks completed by stroke patients, which may affect the results.

In this study, we expect that the cerebellar vermis iTBS can promote the recovery of balance function after stroke. This hypothesis is based on the following evidence.

Maintaining balance depends upon a complex coordination and integration of multiple systems in the body, including the visual system, vestibular system, and auditory system. As pointed out in fMRI research, the cerebellar vermis and the visual network have a strong functional connection (Kellermann et al., 2012; Li et al., 2012). Recent evidence displayed that the vermis coordinates eye and body movements, and provides visual and auditory input related to balance (Fujita et al., 2020). In addition, studies have shown that the vermis participates in regulating vestibular system and maintaining head position (Lam et al., 2016). Balance is best maintained when all inputs are integrated together. Therefore, the cerebellar vermis plays an essential role in the active maintenance of body balance.

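### The post hoc rule leaves its contrasts undefined and, read literally, compares weeks within an arm, which cannot show when iTBS begins to work

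*Protocol article*

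**What the plan says.** Clinical Data Analysis plans a repeated measures ANOVA of BBS, FMA-LE and MBI over weeks 0 to 3. The only follow-up step it gives is that, if the interaction is significant, a post hoc analysis follows and "the Bonferroni adjustment will be used for paired comparisons". It does not say whether arms are compared within a week or weeks within an arm, nor how many comparisons share the adjustment.

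The same section has a general rule for continuous data: "Continuous variables with normal distribution will be described as the mean (standard deviation) and analyzed by an independent-samples *t*-test", with Mann–Whitney U as the non-parametric alternative.

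The fMRI analysis section shows how the authors use the word: "Data will be analyzed by the independent-samples (between-group comparison) or paired (within-group comparison) *t*-test".

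The Discussion states the timing aim: "We want to compare the efficacy at different time points, and to explore the earliest time when the treatment can take effect".

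The Intervention section says: "Patients recruited in this study will receive a 60 min routine rehabilitation treatment immediately after completing real or sham iTBS therapy". That programme is directed at balance, and both arms attend 15 sessions over three weeks.

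**The concern.** Efficacy at a given week of a sham-controlled trial is the difference between iTBS and sham at that week. A comparison of week 1 with week 0 inside the iTBS arm measures the treatment effect plus whatever patients would have gained anyway. These patients are 1 to 6 months after stroke and have balance training at every session, so some gain under sham is plausible.

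If the interaction is significant because of a late effect, within-arm tests can then mark week 1 as significant from recovery that both arms share. Setting a significant result in the iTBS arm beside a non-significant one in the sham arm does not repair this, because it is not a test of the difference between them. What is at stake is a published statement about onset on the primary scale.

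**Working it through.** **1. What the text fixes.** The timing aim needs three between-arm contrasts (weeks 1, 2, 3). The post hoc sentence names none. Its one descriptive word, *paired*, is equated with within-group in the fMRI section. The independent-samples t-test does compare arms, but it is not tied to a visit, to the post hoc step or to the Bonferroni adjustment.

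**2. The plan's own figure.** The Sample Size section gives effect size 0.28, 95% power, alpha 5% and 30 patients. Taking 0.28 as Cohen's f for the group-by-time interaction (2 groups, 4 visits), with correlation 0.5 and sphericity assumed because neither is stated:
- λ = f²·N·m/(1−ρ) = 0.0784 × 30 × 4 / 0.5 = 18.8, on 3 and 84 degrees of freedom.
- Power is 0.959 at N = 30 and 0.944 at N = 28, so 30 reproduces. 30/0.80 = 37.5, rounded up to 38, also reproduces.

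The figure is consistent with sizing for the interaction. It says nothing about contrasts at single weeks.

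**3. Illustration of the within-arm reading.** From the document: 20 per arm, visits at weeks 0 to 3, two-sided 0.05. Assumed, because the document gives no such figures: equal gain of 3 BBS points per week in both arms, SD of change 4, correlation 0.8 between visits, iTBS effect at week 3 only, and Bonferroni over the 4 × 3 / 2 = 6 pairs of visits.
- True between-arm difference at week 1: 3 − 3 = 0.
- Paired test of week 1 against week 0 in the iTBS arm: noncentrality (3/4) × √20 = 3.35, 19 degrees of freedom, alpha 0.05/6 = 0.0083. The probability of significance is 66%.

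The interaction must be significant first. Simulation with that requirement gives:

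| iTBS effect at week 3 | Interaction significant | iTBS arm significant at week 1, all trials | Same, given a significant interaction | Week-1 between-arm test at 0.05/3, given a significant interaction |
|---|---|---|---|---|
| 0 points | 5% | about 3% | 3/5 = about 60% | not tabulated |
| 3 points | about 66% | 43–45% | about 66% | 2–3% |
| 4 points | about 90% | about 60% | about 66% | about 2% |

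In the 4-point case, iTBS is significant at week 1 and sham is not in about 23% of trials with a significant interaction.

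**4. Range.** With the 4-point effect kept, background gain of 1 to 4 points per week and SD of change 3 to 5, the 66% runs from 4% to over 99%, and the 23% from 0.4% to 26%. An unadjusted between-arm test at week 1 stays at 5% to 6.5%.

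**5. Price of the between-arm contrasts.** Power per week at 0.05/3 = 0.0167, noncentrality d·√(n/2), without baseline adjustment; the d values are assumptions:
- 20 per arm: d = 0.5 gives 0.5 × √10 = 1.58, power 19%; d = 0.8 gives 2.53, power 52%.
- 15 per arm: 14% and 38%.

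**The case against.** The strongest reply is that *paired* is loose English for *pairwise*. After a significant interaction, pairwise comparisons would ordinarily include arm against arm at each week, and the section already names a between-arm test for continuous data. This is possible, so it cannot be said that the plan commits to within-arm tests. What stands is that the contrasts and the adjustment family are undefined, and that the literal reading is the one that fails.

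Second, the aim is exploratory, stated in the Discussion. The main hypothesis, recovery of balance function, does not depend on it. That limits the weight of the point.

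Third, the interaction is itself a comparison of the two arms' time courses, and it protects the trial when iTBS does nothing: about 3% overall under the assumptions above. A reader might take the 66% as a false-positive rate for the trial, and the document does not support that. The figure applies when a real late effect exists and only its onset is misdated. Nor does any passage say that onset will be declared from within-arm tests; that would be an inference from the literal wording.

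Finally, detail of this kind often sits in an analysis plan that is not shown. But the article does state a post hoc rule, and the rule as worded does not match the article's own aim.

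**Conclusion.** The point holds as a defect of definition. The post hoc rule does not identify its contrasts; read literally and by the article's own usage, it compares weeks within an arm, and such comparisons cannot establish when iTBS takes effect. The generic independent-samples t-test does not fill the gap.

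The possible error in dating is large if a late effect exists and both arms recover: about 66% against about 2% in the 4-point case. It is small if iTBS has no effect at all. These sizes rest on an assumed gain, SD, correlation and week-3 effect, none of which the document gives, and the range is wide. The overall test of efficacy and the sample size are untouched. The wording should be corrected before analysis, but the point does not threaten the trial's main conclusion.

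**What to change.** State in Clinical Data Analysis that, after a significant interaction, the post hoc contrasts are iTBS minus sham at weeks 1, 2 and 3. Each should be adjusted for baseline BBS and the randomisation stratum (0–20 or 21–40), with Bonferroni over these three (0.05/3 each). Testing in the fixed order week 3, week 2, week 1 is an acceptable alternative. Report within-arm changes descriptively only, and let no statement about onset rest on them.

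This needs no new data, visits or patients, since baseline BBS and stratum are already recorded. The downside is that an early onset becomes harder to claim: with 20 per arm, power at a single week is limited (about 52% even for an assumed d of 0.8), so a non-significant early week should not be reported as absence of effect.
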